#### Use of medical and non-medical health care services

For our health economic evaluation we use the German Questionnaire for Health-Related Resource Use in an Elderly Population (Fragebogen zur Inanspruchnahme medizinischer und nicht-medizinischer Versorgungsleistungen im Alter, FIMA) [45]. We will ask about the type of health insurance, the medication taken in the last 7 days, outpatient visits to the doctor and therapeutic services used in the last 3 months, rehabilitation measures, outpatient operations or stays in day clinics and inpatient treatment in the last 12 months. We will evaluate the answers with calculated unit costs [46]. See Table 2 for measures, assessment, expected scaling and maesurement occasions.

**Table 2 Tab2:**
[figure not shown]
Schedule of enrolment, interventions and assessments

### Participant timeline

Participants fill in the baseline questionnaire at the beginning of rehabilitation. At the end of rehabilitation the participants fill in the first follow-up questionnaire at the rehabilitation center. At the 3- and 12-month follow-ups, participants who completed the baseline questionnaire will receive follow-up questionnaires from the University of Lübeck. Focus groups with some of the participants will be conducted during the intervention as well as three and 12 months after rehabilitation (see Table 3 for a full schedule of enrolment, interventions and assessments).

**Table 3 Tab3:**
[figure not shown]
Schedule of enrolment, interventions and assessments

### Sample size estimation

In order to ensure a 20% increase in the proportion of rehabilitants with stable return to work per rehabilitation center (CPR: 40%; WMR: 60%; power: 80%; level of significance: 5%), an analysis sample of 194 persons (i.e. 97 persons per intervention arm) is necessary. Although we will use multiple imputations to perform an intention-to-treat analysis, we increase the sample size to compensate for the potential loss of participants during our follow-up assessments. This ensures sufficient power even if only complete cases are analyzed. Assuming a response rate of 65% after 1 year, we will recruit 300 patients per rehabilitation center. In a total sample of 1800 patients, a minimal difference of seven points can be detected. In a total sample of 1164 patients (response rate of 65%), a minimal difference of eight points can be detected (Fig. 1).

**Fig. 1 Fig1:**
[figure not shown]
Flow of participants

Of the 1800 persons recruited, eight patients from each of the intervention and control groups are supposed to take part in interviews for a panel study. The patients should be in the third week of their rehabilitation program. The second and third follow-up interviews will be conducted with three persons from these focus groups. The focus groups with the team members are planned with five persons per rehabilitation center. The number of participants in the focus groups with the team leaders will depend on the number of teams per rehabilitation center.

### Recruitment

The rehabilitation centers check all newly arrived rehabilitation patients with mental disorders between the ages of 18 and 60 years to see whether they have an increased risk of not returning to work. This will be detected using the SIMBO-C [24]. In the case of a positive result (i.e. a score of at least 27 points), the study assistant informs the person about the trial. The study assistant hands out the study documents to the patient. An information letter details the content and objectives of the study as well as the patient’s personal rights regarding the handling of personal data. In case of participation, the patients endorse informed consent and complete the baseline questionnaire. If one of the follow-up questionnaires is not returned, a questionnaire will be sent again, with a reminder to all participants after 3 weeks.

Recruitment for the interviews will be carried out by the study assistants in the rehabilitation centers. Informed consent forms are handed out during the recruitment process and can be discussed with the person carrying out the interview if necessary and will be signed before the first interview. However, the teams, team leaders and medical directorates will be recruited by the person conducting the interviews.

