### Trial design

The study is a randomized controlled trial with two parallel groups. Participants are randomly assigned to a WMR or CPR group in a one-to-one ratio. Focus groups and individual interviews supplement our study with qualitative data.

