### Secondary outcomes

Secondary outcomes cover several dimensions of health, functioning and coping strategies (see below) and will be measured at all four measurement points. At the first follow-up after completing the rehabilitation program, participants will also appraise how the rehabilitation programs dealt with work-related issues and how satisfied they were with the treatment.

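### The stated answer to non-return is a repeat mailing and a reminder; a one-page form at 12 months, holding only the return-to-work items, could cheaply recover part of the planned 35% loss of primary outcomes

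*Protocol article*

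**What the plan says.** All references are to the protocol article.

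- **Follow-up route.** Under Participant timeline, the university sends the 3- and 12-month questionnaires to participants. For non-return, Recruitment says: "If one of the follow-up questionnaires is not returned, a questionnaire will be sent again, with a reminder to all participants after 3 weeks".
- **Expected loss.** Sample size estimation says: "Assuming a response rate of 65% after 1 year, we will recruit 300 patients per rehabilitation center". Data collection and Statistical methods (Treatment effect) then impute what is missing.
- **Primary outcome.** Under Primary outcome, stable return to work means being employed for at least 4 weeks with no sick leave at follow-up. A few questions settle this.
- **What travels with it.** Secondary outcomes "will be measured at all four measurement points", and the sections that follow describe five named instruments.
- **Other routes.** Outcomes and other measures names patient questionnaires and discharge letters as sources. A letter written at discharge cannot carry work status 12 months later. Telephone and video contact with patients appears only for the small qualitative panel (Data collection; Focus groups and interviews).
- **Blinding.** Nobody is blinded.

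**The concern.** The shortest and most important items appear to share the return rate of the whole booklet. The plan accepts a 35% loss and answers it with more patients and with imputation. More patients restore precision. They do nothing about bias if patients who do not reply differ from those who do in ways the observed data do not explain.

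That is plausible here. Patients know their program, they are selected for a high risk of not returning to work, and willingness to fill in a long form may depend on work status or on arm. Returned booklets alone cannot show whether this has happened. A short form sent to people who did not return the booklet would leave fewer outcomes to imputation and give some direct evidence on that group.

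**Working it through.** **1. The plan's own figures.** The inputs in Sample size estimation are "CPR: 40%; WMR: 60%; power: 80%; level of significance: 5" per cent, with 1:1 allocation. Sidedness is not stated; a two-sided test with pooled variance and no continuity correction gives

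n per arm = [1.960 × √(2 × 0.5 × 0.5) + 0.842 × √(0.4 × 0.6 + 0.6 × 0.4)]² / 0.20² = (1.386 + 0.583)² / 0.04 = 96.9, so 97.

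This matches the text: "an analysis sample of 194 persons (i.e. 97 persons per intervention arm) is necessary". Then 194 / 0.65 = 298.5, so 299 against 300 planned, and 6 × 194 = 1164 against 0.65 × 1800 = 1170. From a 40% control rate at 80% power, the detectable difference is 8.1 points at 1164 or 1170 (stated: eight) and 6.5 points at 1800 (stated: seven). The sample size reproduces.

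**2. Length of the booklet.** Work Ability Score 1 + SF-36 36 + HEALTH-49 modules (18 + 7 + 5) + job anxiety 13 + ReRe 20 = 100 items, before the employment questions and any questions on health-care use. Table 2, which gives content by occasion, is not shown, so the 12-month content is inferred.

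**3. Outcomes not observed.** 0.35 × 1800 = 630.

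**4. Exposure to bias.** With equal response in both arms, the pooled difference is 0.65 × (difference in responders) + 0.35 × (difference in non-responders). If the second term is imputed wrongly by δ points, the estimate shifts by 0.35 × δ:

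- δ = 10 (assumption): 3.5 points
- δ = 20 (assumption): 7.0 points
- a shift of 20 points would need δ = 20 / 0.35 = 57 points

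**5. Effect of a short form.** The documents give no recovery rate, so a range is assumed. With recovered share f, response = 0.65 + 0.35 × f. The last column further assumes that those still missing keep a 20-point departure.

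| f (assumed) | Response | Observed N | Left to imputation | Detectable difference | Shift if δ stays 20 |
|---|---|---|---|---|---|
| 0 | 65% | 1170 | 630 | 8.1 | 7.0 |
| 10% | 68.5% | 1233 | 567 | 7.9 | 6.3 |
| 25% | 74% | about 1327 | about 473 | 7.6 | 5.25 |
| one third | 77% | 1380 | 420 | 7.5 | 4.7 |

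**6. Limit of the last column.** Suppose a quarter of non-responders reply and turn out to be just as the imputation would have predicted. All the departure then sits in those who never reply: it is 7.0 / 0.2625 = 26.7 points in that group, and the shift remains 0.2625 × 26.7 = 7.0.

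**The case against.** The strongest reply is that this is a preference about retention, not an error. A journal article often leaves mailing logistics to the full protocol, and the text does not say that nothing further will be done. That limits the strength of the point. It does not remove it: the article does fix a procedure for non-return, and the suggestion adds to that stated rule.

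Four stronger readings are tempting, and the document does not support them.

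- **That the same booklet is sent again.** The text says only that a questionnaire is sent. The full booklet is the natural reading, but it is an inference.
- **That non-response could create or hide an effect as large as the one the trial is sized for.** The trial is sized for 20 points per center. A 7-point shift is about a third of that, and it is also below the eight points detectable in the pooled responders.
- **That a short form cuts the bias in proportion to the outcomes recovered.** Step 6 shows this holds only if the remaining non-responders are no more atypical than those recovered.
- **That 35% will be lost.** The 65% is a planning figure, and the text does not say whether it already counts returns after the reminder.

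Existing safeguards also count. Return to work is asked at 3 months, the end-of-rehabilitation questionnaire is completed on site, and baseline scores are covariates. All of these can feed the imputation, although the article does not list its variables. A 20-point departure would have to remain after conditioning on whatever is used. The gain in precision is small, about 0.2 to 0.6 points. Finally, a late form would measure a different 4-week window unless it names the original date; the fix has to deal with that.

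**Conclusion.** The point holds as an optional, low-cost improvement. The sample size stands, and the trial is not invalid without the change. The stated follow-up leaves about 630 of 1800 primary outcomes to imputation in an unblinded trial, with no stated step aimed at the primary outcome alone. At an assumed 20-point departure this exposes the pooled estimate to a 7-point shift, which is close to the pooled detectable difference of eight; at 10 points it is 3.5. The main benefit of a short form would be fewer imputed outcomes and some evidence on initial non-responders; better precision comes second.

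This rests on four assumptions: the 65% response is realized, and about equally in both arms; the 12-month booklet is as inferred from the instrument descriptions; 10% to one third of non-responders return one page; and, for any fall in bias, those still missing are no more atypical than those recovered.

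**What to change.** At 12 months only, when the repeat mailing has also gone unanswered, send a single page with just the items that define stable return to work.

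- Ask about the 4 weeks before the original 12-month date, and print that date on the form, so that a late reply measures the same window as the booklet.
- Count the reply as the primary outcome.
- Keep the full booklet for the first two mailings, so that nobody who would return it is diverted.
- Report response by arm and by mailing.
- Compare the late returns with the values the imputation would have given them, by arm.

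The cost is one extra mailing to at most about 630 people and a short ethics notification. The downsides are that these returns bring no secondary outcomes and that the recall period is slightly longer. Randomization, the endpoint definition and the sample size do not change.

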### Allocation

A separate randomization sequence is created for each rehabilitation center by the University of Lübeck. For the computer-generated randomization lists, blocks of four and eight are combined in order to guarantee balanced case numbers, even if the lists cannot be processed completely. The randomization envelopes are sealed and will be opened in the rehabilitation centers after informed consent of the participants is determined. After arriving at one of the six study centers, the potential study participants are informed in detail about the study, both orally and in writing, and are asked to participate by the study assistants, who have been trained by the research team. In particular, the potential participants are informed that there will be two different study groups (intervention group and control group) and that allocation to the two groups will be randomized.

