### Primary outcome

The primary outcome of this study is stable return to work 12 months after rehabilitation. Return to work will also be assessed at the three-month follow-up. Stable return to work has been defined in accordance with Kuijer and colleagues [34] as a minimum of 4 weeks of employment without sick leave at follow-up.

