### Blinding

No one will be blinded before, during or after the trial as the realized rehabilitation program will be recognizable for all stakeholders.

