### Data collection

Outcomes and other measures will be assessed with patient questionnaires or will be extracted from the rehabilitation discharge letters (see Table 2). For participants who do not complete follow-up questionnaires, missing data will be imputed. If participants withdraw their participation, the collected data will be deleted.

Three consecutive interviews with participants of the complementary panel study are planned. The first interviews will take place during rehabilitation in the rehabilitation centers as focus groups. After three and 12 months, follow-up interviews with the same sample will be conducted as individual interviews by telephone or video call. Furthermore, members of the multi-professional teams, team leaders and the respective medical directorate of each rehabilitation center will be interviewed. Again, the first interviews will be conducted in the rehabilitation centers and the second interview after 6 months by telephone or video call. The interviews of teams and team leaders will be conducted as focus groups.

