### Statistical methods

#### Treatment effect

We use random-effects models to take into account that different true effects are possible in different rehabilitation centers. Linear models will be used for continuous outcomes and logistic models for binary outcomes. Baseline scores of outcomes will be included as covariates. Possible differences in effects at the level of the rehabilitation centers may be associated with WMR or CPR implementation. In order to test an effect modification due to the implementation of either WMR or CPR, subgroups are formed based on the received treatment dose (content, consistency, achievement of objectives) and the work-related treatment dose delivered. To reduce the number of subgroup analyses, the mean differences between WMR and CPR for dose delivered and dose received are used to categorize the subgroups (high distinguishability vs. low distinguishability). We assume that greater distinguishability of both interventions based on treatment dose delivered and received is associated with higher effects. Further characteristics of the rehabilitation centers for subgroup analyses may derive from the focus groups. Gender, age, migration background and education are examined as possible moderating patient characteristics. Multiple imputations will be used to fill in missing data and to perform an intention-to-treat analysis.

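### The protocol does not tie envelope opening to a returned baseline questionnaire, yet sends the 3- and 12-month questionnaires only to baseline completers, so primary-outcome follow-up could depend on the known arm

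*Protocol article*

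**What the plan says.** All references are to the protocol article.

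- **Allocation** gives the trigger for revealing the arm: "The randomization envelopes are sealed and will be opened in the rehabilitation centers after informed consent of the participants is determined".
- **Recruitment** names consent and the questionnaire together: "In case of participation, the patients endorse informed consent and complete the baseline questionnaire". It does not say where envelope opening falls relative to the questionnaire.
- **Participant timeline** gives the timing of baseline: "Participants fill in the baseline questionnaire at the beginning of rehabilitation". For the 3- and 12-month assessments it adds that "participants who completed the baseline questionnaire will receive follow-up questionnaires from the University of Lübeck". The end-of-rehabilitation questionnaire is filled in at the center and carries no such condition.
- **Primary outcome**: "The primary outcome of this study is stable return to work 12 months after rehabilitation".
- **Treatment effect**, under Statistical methods: "Baseline scores of outcomes will be included as covariates". The same section plans multiple imputation for an intention-to-treat analysis.
- **Blinding**: "No one will be blinded before, during or after the trial".
- **Data collection**: "Outcomes and other measures will be assessed with patient questionnaires or will be extracted from the rehabilitation discharge letters". It plans imputation for people who do not complete follow-up questionnaires. It does not mention randomised people who are never sent one because they have no baseline form.

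**The concern.** Two stated rules combine badly. The first lets the arm be revealed once consent is given. The second decides who is asked for the primary outcome, and its criterion is completion of a form that the text does not place before allocation. Read literally, a patient can consent, be randomised, learn the arm, leave the baseline form incomplete, and then never be sent the 12-month questionnaire.

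Nobody is blinded, so willingness to fill in the form may differ between patients given the work-related program and those given the conventional one. Follow-up of the primary outcome would then be restricted on an event that can occur after randomisation and can depend on arm. Randomisation no longer protects the comparison among those followed, and imputation has to repair a gap that the plan itself created.

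There is a secondary exposure. If the form is filled in after the arm is known, subjective baseline scores (work ability, quality of life, psychosocial health, job anxiety) may already reflect the reaction to allocation. Adjusting for them would remove or add part of a difference that is not a baseline difference.

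**Working it through.** **1. The plan's own figures.** Inputs from Sample size estimation: 40% versus 60%, power 80%, significance level 5% (two-sided assumed, as the article does not say).

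n per arm = [1.96·√(2·0.5·0.5) + 0.8416·√(0.4·0.6 + 0.6·0.4)]² / 0.2² = (1.386 + 0.583)² / 0.04 = 96.9, so 97.

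This matches the stated 97 per arm and 194 per center. 194 / 0.65 = 298.5, so 299, against 300 planned. 6 × 194 = 1164 analysed, or 582 per arm. These figures reproduce, and the point does not alter them.

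**2. The order of steps, by case.**

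| Order in practice | Effect of the mailing rule | Baseline covariates |
|---|---|---|
| Baseline form always returned before the envelope is opened | Excludes no randomised patient | Measured before allocation |
| Envelope opened on consent, baseline form later | Any randomised patient without a form is not asked for the primary outcome | May react to the known arm |

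The readable text permits both rows. Allocation names consent alone, Recruitment lists consent and then the questionnaire, and Participant timeline gives a window that can fall on either side of allocation.

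**3. What non-completion would cost.** Each 1% of randomised patients without a baseline form is 0.01 × 1800 = 18 patients not asked for the primary outcome. The article gives no non-completion rate. It is zero in the first row of the table.

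**4. Illustration for the primary outcome.** None of these inputs is in the documents except the 40% rate and the 582 per arm. Assume no true effect, 40% return to work in both arms, non-completion of a fraction L in the conventional arm only, and a return-to-work rate q among those non-completers. The rate among those still followed is (0.40 − L·q) / (1 − L).

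- L = 5%, q = 60%: 0.37 / 0.95 = 38.9%. Spurious difference 1.1 points. With 582 and 553 followed, the standard error is √(0.24/582 + 0.389·0.611/553) = 0.0290, and the two-sided type I error is 6.5%.
- L = 10%, q = 60%: 0.34 / 0.90 = 37.8%. Spurious difference 2.2 points, type I error about 12%.
- L = 10%, q = 20%: 0.38 / 0.90 = 42.2%. Spurious difference −2.2 points, type I error about 12%.

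The direction therefore depends on who fails to complete. For scale, the plan states a detectable difference of 8 points at 1164. These figures are for the followed patients alone, and imputation with informative predictors could reduce them.

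**5. Illustration for a secondary scale.** If learning the arm shifts the mean baseline score by d SD between arms, and the slope of outcome on baseline is b, the adjusted effect moves by b × d. With assumed d = 0.1 to 0.3 and b = 0.5 to 0.7, the bias runs from 0.5 × 0.1 = 0.05 to 0.7 × 0.3 = 0.21 SD. A simple two-arm standard error at 582 per arm is √((1 − b²)·2/582) = 0.051 (b = 0.5) or 0.042 (b = 0.7). The planned random effects for six centers could make the true standard error larger. A shift of that size also requires many patients to answer after learning their arm, which is exactly what the text leaves open.

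**The case against.** The strongest reply is that the text has a natural, harmless reading. Recruitment puts consent and the baseline questionnaire in one step, and Allocation comes afterwards in its own section. Saying that the envelope is opened after consent rules out opening it before consent; it does not say that it is opened before the questionnaire. Fig. 1 and Table 3, where the order of enrolment, baseline and allocation could well appear, are not shown. If baseline comes first, both problems vanish. This stands: the finding is an order left open, and a reader who infers that baseline is measured after allocation goes further than the article does.

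Three other inferences are tempting and are not supported.

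- **That a patient without a baseline form is lost altogether, with nothing to impute from.** The end-of-rehabilitation questionnaire has no baseline condition. The SIMBO-C score is obtained at screening (Eligibility criteria, Recruitment), arm and center are known, and discharge letters give delivered dose and the socio-medical assessment. None of these records return to work at 12 months, but they can inform imputation.
- **That the intention-to-treat claim is contradicted.** Imputation can keep such patients in the analysis set. The claim is weakened, because the missing outcomes are produced by a rule tied to an event that may depend on arm.
- **That every adjusted effect is biased.** The baseline counterparts of the primary outcome are employment status and sick leave over the previous 12 months. These are largely factual and should react far less to allocation than symptom or attitude scales.

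What the objection does not remove is the mailing rule itself. It is stated outright and governs the primary outcome. If completion were guaranteed before randomisation, it would exclude no randomised patient, so it has an effect only where it does harm.

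**Conclusion.** The point holds as a moderate one. Consent is the only stated condition for opening the envelope, and no readable text requires the baseline form first. The 3- and 12-month questionnaires are expressly limited to baseline completers. Should any randomised patient lack a baseline form, the primary outcome is not sought for that patient, on a condition that can depend on the known arm.

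The size cannot be derived from the document. On the assumed values above, the primary comparison moves by about 1 to 2 points in either direction, with type I error of about 6.5% to 12% before any gain from imputation. A covariate reaction could move a secondary scale by 0.05 to 0.21 SD. Both ranges rest on assumed inputs and fall to zero if baseline always precedes allocation. It would be wrong to quote them as expected biases, or to rate the matter as a defect that must be repaired before the trial can be interpreted. The textual gap is certain; its consequence is not.

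**What to change.** 1. **Participant timeline.** Replace the restriction with wording such as: All randomised participants who have not withdrawn are sent the 3- and 12-month questionnaires, whether or not the baseline questionnaire was completed. This is the more important change, because it protects the primary outcome whatever the order of steps at the centers. Missing baseline scores can then be handled by the imputation already planned.
2. **Allocation.** Add wording such as: The envelope is opened only once consent has been signed and the completed baseline questionnaire has been handed to the study assistant; the date and time of each are recorded.

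If recruitment has begun, the first change can still apply to everyone not yet followed up. For patients already enrolled, report by arm how many had no baseline form and, where known, how many completed it after allocation.

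The cost is two sentences, an instruction to study assistants, a short delay before some envelopes are opened, and a few more mailings. The sample size does not change. If the centers already collect the baseline form first, the second change only records existing practice.
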